#### Recruitment

The 24 teams that will be targeted for this intervention compete in the Malawi Super League, which is the highest organised league for women’s football in Malawi. The level of football is amateur, as is most women’s football in LMICs. However, the league produces many of the players for the national teams. The teams in the league are divided into eight (8) teams each by geographical region into the Northern, Central and Southern regions. The distribution of teams into the two arms per region is shown in **Fig 2** below.

**Fig 2 pone.0278428.g002:**
[figure not shown]
FIFA football nurse recruitment strategy for participating teams in the Malawi Women’s Super league.

While medical resources required for football training and matches are known, most teams do not have medical support available to them either on a part-time or full-time basis. The 24 teams will be recruited and monitored for the 2022/2023 football season. The nurses will be approached through their District Health Officers (DHOs) while the teams will be approached through the country’s football governing body; Football Association of Malawi (FAM) and their specific District Sport Officers (DSOs) as is regulated in Malawi. A presentation on the trial will be made to the various DHOs, DSOs, and FAM by one of the investigators (EC), after which representatives from the teams will be invited to attend a presentation on the study protocol, where they will be invited to participate in the study in either the INT or CON group. The inclusion and exclusion criteria for the trial are as shown in **Table 2.**

**Table 2 pone.0278428.t002:** Inclusion and exclusion criteria for nurses, women’s football teams and physiotherapists/doctors for the FIFA football nurse trial.

Inclusion criteria	Exclusion criteria
Women’s football clubs in the Women’s League in Malawi registered with the Football Association of Malawi (FAM).	Women’s football clubs in the Women’s League in Malawi that already have medical personnel attached to their team.
Nurses registered with the Nurses and Midwives Council of Malawi with at least 3 years post graduate experience.	For potential supervisors, less than 3 years post qualification experience; incomplete FIFA Medical Diploma.
Physiotherapists with a recognised university qualification in physiotherapy, registered with the Medical and Dental Council of Malawi and with at least 3 years post graduate practice experience.	For potential Football Nurses, less than 3 years of post-qualification experience.
Medical doctors with a recognised university qualification (e.g., MBChB/MBBS) registered with the Medical and Dental Association of Malawi and at least 3 years post graduate practice experience.	For potential Football Nurses and supervisors, current attachment to a Women’s Football club in Malawi’s Women’s League
(for physiotherapists and medical doctors) Completion of the online FIFA Medical Diploma prior to the commencement of the project.	

Once the team has confirmed their participation, all the players registered for the team in the 2022/2023 season will be eligible to participate and will be recruited through the team. Verbal and written assent (players under 18) and consent (in English or Chichewa) from the nurses, players, and technical personnel will be required for each participant before the they can be included in the trial as mandated by Malawian research ethics and government statutes.

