### Trial design and study arms

#### Trial design

This study will be a cluster randomised controlled trial. This design is applicable as it allows for a field-based intervention to be implemented for one competitive season while decreasing the chances of contamination between the groups. African women’s football is the sport that has been chosen as it is the most commonly played women’s team sport on the continent and therefore, is a priority sport for improving medical care at and from grassroots levels. Adherence to the FIFA Football Nurse program; football exposure data; injury, illness and medication use surveillance and the in this trial will be similar to those used in previous football studies [35, 37] and conform with the definitions and data collection procedures outlined in the latest injury consensus statements [36]. The study will also include a qualitative evaluation of the participants’ (players, coaches, nurses) experience of the FIFA football nurse program.

All the 24 women’s teams in the Malawi Women’s Super league will be randomly assigned in a 1:1 ratio to either the Football Nurse intervention (INT–12 teams) or the control group/standard care (CON–12 teams) through a random draw. For the allocation schedule for random assignment to each arm, the names of the 24 teams will be placed in three (3) bowls, a bowl for each region. They will then be picked consecutively and alternately, and allocated into the INT and CON groups by one of the investigators ([name]). This will be done after the training of the nurses and after each team (cluster) have agreed to be a part of the study. For transparency, the random draw will be conducted in the presence of representatives from the football association and will be video and audio- recorded.

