#### Control or standard care

In the control or standard care group (CON) consisting of 12 teams (clusters), each team will have 30 registered players, one (1) team manager, and one (1) coach and will continue their SEM practise ‘as per usual’. A member of the research team will contact a designated member of their technical personnel to collect data on football exposure; injury, illness and medication use surveillance after each training session and league match. Beyond this, the teams in the CON group will not receive any special instructions. It is noteworthy that the teams in the CON and INT groups will at some point in the season play against each other and the Football Nurse will be duty bound to render care should a player from the CON group be injured or fall ill during the match. Therefore, contamination cannot be entirely avoided.

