#### Sample size

The study aims to evaluate the impact of the Football nurse intervention on team sports medicine practice. Hence, the study will recruit twelve (12) nurses, with one assigned to each intervention team, and six (6) physiotherapists and/or doctors to supervise the Football Nurses from two teams each.

To determine the appropriate sample size, the study used the cluster randomized formula as in previous studies [38]. This formula considers the intra-cluster correlation coefficient, number of participants, expected effect size, and power of the study. The formula is as follows:

$$C=1+{\left(Z_{\alpha /2}+Z_{\beta }\right)}^{2}\frac{\left[\sigma_{0}^{2}+\sigma_{1}^{2}\right]\times [1+(m-1)k]}{m{\left(\mu_{0}-\mu_{1}\right)}^{2}}$$

Where C is the number of clusters required per treatment arm, *Z*_*α*/2_ and *Z*_*β*_ are the critical values of the standard normal distribution for the desired confidence level and power, respectively, *m* is the number of individuals per cluster and *k* is the intracluster coefficient, *μ*_1_ and *μ*_0_ are the true means, and σ_1_ and σ_0_ are the standard deviations, of the outcome variable in the presence and absence of the intervention, respectively.

The design effect of a CRT is related to the intracluster correlation coefficient as follows:

DEFF=1+(m−1)k

Assuming a 95% confidence level (*Z*_*α*/2_ = 1.96), a power of 80% (*Z*_*β*_ = 0.84), an expected effect size of 0.19 (based on a 50% increase in team sports medicine practice), a standard deviation of 0.30, an intra-cluster correlation coefficient of *k* = 0.2, and 25 participants per cluster, the study estimates that it will need 12 clusters (teams) in both the control and intervention groups. Therefore, a total of 600 participants will be recruited, with 300 participants in each group. In summary, the study will recruit twelve (12) nurses and six (6) physiotherapists/doctors to supervise the intervention teams. The study will need 12 clusters (teams) in both the control and intervention groups, with a total of 600 participants (300 in each group) to detect a statistically significant change in team sports medicine practice at a 95% confidence level and 80% power, using the cluster randomized formula [38, 39].

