*Adherence*. This study has been designed to be optimally implemented in grassroots women’s football in a low-income setting. The researchers will monitor adherence of the nurses’ attendance at training sessions and matches using electronic record sheets. These records will then allow for exposure hours to be calculated and a measure of adherence to be determined. The surveillance data will be monitored on a biweekly basis to ensure it is up to date and following standardised operating procedures. The study is being performed in a league that has massive shortages of medical personnel and therefore, the participants in the intervention group will be motivated to adhere to the protocol as best they can.

*Ethical considerations*. Permission was sought and obtained from FAM and Directors of District and Social Services (DHSS) in all the regions where the women football teams are based. Ethical approval for this trial was obtained from the College of Medicine Research and Ethics Committee (COMREC), Blantyre, Malawi (protocol number: P.01/22/3551). The study will be conducted in accordance with the Declaration of Helsinki, the protocol and GCP guidelines. Before they can be a part of the study, and before randomisation, the investigators will explain the objectives of the study to the physiotherapists, doctors and nurses; football teams, their women players, and their coaching teams. They will only then be eligible to be included in the randomisation and eventual participation in the study after they have provided verbal and written assent and consent. This study will be voluntary, and participants will be informed that they have a right to participate or to withdraw from the study at any time, without prejudice. Data collected from the study will be stored in a password protected database and computer and that will only be accessible to the researchers. Study participants will be assured of their confidentiality. The names of the participants will only be on the consent form and in all other instances, they will be referred to by their assigned unique code.

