*Patient and public involvement*. Patients and the public were not involved in the design of this protocol. However, various stakeholders in Malawi women’s football (e.g., nurses, women football players, district sports officers, district representatives in women’s football) will be consulted on the conduct, reporting, and dissemination plans for the research.

*Project time frame*. This project will be performed over an 8-month period during the 2022/2023 football season (May to December).

May 2022 –training of nurses; recruitment of football teams; randomisation of teams.June 2022 –baseline testing of teams (assessment of injury behaviours, team medical practice, injury risk, nutritional data, and mental health assessment)June 2022 to December 2022 –implementation of the football nurse intervention; injury surveillance; adherence and exposure data collection.October 2022 –midway testing of teams (assessment of injury behaviours, team medical practice, injury risk, nutritional data, and mental health assessment)December 2022 –final testing of teams (assessment of injury behaviours, team medical practice, injury risk, nutritional data, and mental health assessment); semi-structured interviews with sample of players and coaches from both groups and all nurses

*Outcomes and significance*. We expect to develop a low cost, sustainable and context relevant solution to manage the treatment gap of football injuries/illnesses in underserved communities such as women’s football. Through the study, we also anticipate the development and maintenance of player health, injury and illness monitoring databases for Malawian women football players in club football, which can be replicated in grassroots women’s football leagues in LMICs. This will allow the monitoring of trends and development of relevant preventive or management strategies in these settings. Additionally, we expect this study to lead to the development of a flagship model which can inform implementation of similar task sharing approaches to SEM practice in other LMICs in Africa and globally.

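### Player eligibility has no cut-off at the draw, so the plan permits enrolment once the arm is known, against its own rule of consent before randomisation

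*Protocol article*

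**What the plan says.** Four places in the protocol article bear on when a player enters the trial.

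- **Recruitment.** The eligibility rule is that "all the players registered for the team in the 2022/2023 season will be eligible to participate and will be recruited through the team". The point from which this applies is team agreement, not the draw. Assent or consent "will be required for each participant before the they can be included in the trial". No registration or enrolment cut-off is given, and this consent sentence does not mention the draw.
- **Trial design.** Teams are drawn after the nurses have been trained and "after each team (cluster) have agreed to be a part of the study". Individual player consent is not named as a condition. The draw is witnessed by football association representatives and recorded.
- **Project time frame.** After nurse training, the May 2022 entry lists "recruitment of football teams; randomisation of teams". Baseline testing is in June, and the season and surveillance run to December. No step or date is given for enrolling players.
- **Ethical considerations.** The study is explained before randomisation to the supervisors, nurses, teams, women players and coaching staff. Then: "They will only then be eligible to be included in the randomisation and eventual participation in the study", with verbal and written assent and consent as the condition.

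**The concern.** In a cluster trial, randomising teams balances the arms in expectation only for players whose membership of the study is settled before allocation, or whose later entry does not depend on it. If a player decides whether to consent, or registers with a team, once it is known whether that team has a nurse, the two groups of players can differ for reasons unrelated to the intervention. Injury history, interest in medical care and willingness to report are plausible examples.

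The arm cannot be concealed here: the draw is open, and the Blinding section accepts that intervention teams will know they have a nurse. The order of consent and draw is therefore the main safeguard. One section states that order, and the sections staff would follow in running the trial do not carry it through.

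**Working it through.** The point concerns the order of events, and the plan has no figure of its own to reproduce. The check is to take each kind of player and ask what each rule says of her.

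**Inputs**

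- Eligibility: registered for the team in the 2022/2023 season (Recruitment).
- Start of player recruitment: team confirmation (Recruitment).
- Conditions for the draw: nurse training and team agreement (Trial design).
- Date of the draw: May 2022. Season: May to December (Project time frame).
- Player consent: before inclusion in the trial (Recruitment); before inclusion in the randomisation (Ethical considerations).

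**Three cases**

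| Player | Recruitment, Trial design and Project time frame | Ethical considerations |
|---|---|---|
| A. Registered and consented before the draw | May enter | May enter |
| B. Registered before the draw, consents after it (for example at June baseline testing) | May enter: team agreement is enough for the draw, and consent need only precede her inclusion | Barred: no consent before randomisation |
| C. Registers after the draw, within the season | May enter: registered in the 2022/2023 season | Barred: cannot have consented before randomisation |

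Case A raises no difficulty. In case B the rules can be reconciled if staff apply the ethics rule on top of the others, but nothing in the draw conditions or the timeline makes them do so. In case C the two rules cannot both be met. June to December, seven of the eight project months, lie after the draw, so the calendar leaves room for case C.

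**Which outcomes are exposed**

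- Injury prevention behaviours, intrinsic injury risk, nutrition and mental health are measured on individual players. The logistic regression compares the proportions of players injured, ill or taking medication. These depend directly on who is enrolled.
- Injury, illness and medication rates are calculated for all players per 1000 hours, so they too depend on who is counted.
- The primary outcome is evaluated at team level. However, its questionnaire covers players' and coaches' sources of medical information and self-reported knowledge. The Data analysis section takes a mean (SD) by cluster, and the Sample size section uses 25 participants per cluster with an intracluster correlation of 0.2. If the team score averages player responses, enrolment can move it. If it is one team-level return, this route is closed.

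**Size**

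Suppose a fraction p of an arm's analysed players entered after the draw, and they differ on average by d from that arm's other players for reasons of selection. The arm mean then shifts by p × d, and the bias in the difference between arms is p₁d₁ − p₀d₀. The document gives neither p nor d for either arm, so no number follows.

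**The case against.** The strongest reply is that the sections can be read as one sequence. Recruitment starts from team confirmation, team confirmation precedes the draw, and the ethics text puts player consent before randomisation. The order is then team agrees, players consent, draw. Team agreement is a necessary condition for the draw and does not say that players may consent later. The time frame is only a list by month. This stands in part: no sentence says that players are recruited after the draw, and for players who consent before it there is no contradiction. It does not remove case C, and it leaves case B dependent on staff importing a rule that the draw conditions omit.

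A second reply is that registration in the season may simply mean the season's roster, and that mid-season registrations and transfers are never mentioned. That is fair. Late entry is a possibility the wording leaves open, not something the plan describes.

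A reader might also infer that teams choose whom to put forward, because "each team will have 30 registered players" gives 24 × 30 = 720 players while the Sample size section says "a total of 600 participants will be recruited, with 300 participants in each group". The documents do not support this. All registered players are eligible, no text lets a team pick 25 of its 30, and 25 may be a planning figure that allows for non-consent. A bias estimate built on that gap would not measure late entry either.

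Third, the nurse covers the whole team, and no text makes her care depend on enrolment, which weakens the incentive to enrol for the sake of a nurse. The plan also adjusts for previous injury, age, experience and BMI. Both points lessen the concern. Neither deals with unmeasured willingness to consent or report.

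Last, handling of late registrants could be left to a fuller document. The conflict between two stated entry rules is in this text and can be settled here.

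**Conclusion.** The plan permits, but does not prescribe, enrolment of players once the arm is known, and this conflicts with its own requirement that players are informed and consent before randomisation. The conflict is certain for a player who registers after the draw. For a player already on the roster it depends on which section staff follow.

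The consequence is a risk of differential consent or registration by arm. It bears mainly on the player-level secondary outcomes and on the injury, illness and medication comparisons. It extends to the primary score only on the assumption that the score averages player responses, which the text suggests but does not state. The size cannot be given, because the number of late registrants and their difference from other players are not in the document. A reader might go further and conclude that post-draw recruitment is the plan. The wording does not support that, since recruitment is tied to team confirmation, which comes first.

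**What to change.** Reconcile the Trial design, Recruitment and Project time frame sections with the Ethical considerations section:

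1. In Trial design, add a condition for the draw: in all 24 teams the player roster has been fixed and player consent (or assent) has been completed.
2. In Recruitment, replace the open-ended season wording with a cut-off at the draw. Define the population for between-arm comparisons of player-level outcomes as players registered and consented before the draw, analysed in the team they belonged to at the draw.
3. In the Project time frame, add a player-consent step in May, before randomisation.
4. State that players who register later may enter surveillance but are reported separately from the main comparison.

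This applies a rule the plan already contains. It concerns entry and analysis only and does not alter the care any player receives. The cost is a change of wording, an explicit order of steps within May, and slightly fewer players in the main comparison.

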#### Blinding

However, participants will not be aware of the entire ‘true’ purpose of the trial. They will be informed that they are being allocated a Football Nurse so that we can study the feasibility of this project in alleviating shortage of medical support in women’s football. Likewise, the INT group cannot be blinded as they will be aware of the Football Nurse assigned to them. However, the data will be coded and blinded before it can be analysed statistically.

#### Standardisation of procedures

The physiotherapists and doctors will complete the modules from the freely and publicly available online FIFA Medical Diploma before the trial commences. This will allow for uniformity of football medicine practice and supervision among the participants during the trial. Shortly before the football season begins (1 week before), all the nurses and the physiotherapists/doctors will undergo a one (1) day training on emergency pitch side football medicine using the latest version of the FIFA Emergency Care training manuals. This training will be conducted by experienced sports medicine personnel ([name] and EC) as well as experienced trainers in basic life support (BLS) and first aid from the Departments of Emergency and Orthopaedics at KUHeS. Further, all research personnel will receive half a day’s training on the online data capturing system that will be used for the study. The research team will have access to written standard operating procedure on their mobile data collection devices as well. The team will also meet every fortnight to catch up and ensure adherence to standard research procedures.

The football nurse attached to each team will be primarily responsible for data collection for the INT teams and the research team, through a designated individual in the football team, will be responsible for data collection for the CON teams.

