## Materials and methods

### Football nurse intervention

The purpose of this study will be to evaluate the effect on teams’ sports medicine practice of randomising women’s football teams to a trained general nurse as a pitch side responder or usual practice. This study will be a cluster randomised control trial, whose reporting will follow the Consolidated Standards of Reporting Trials (CONSORT) 2010 statement: extension to cluster randomised trials [34]. Clusters will be registered teams in the Women’s Football League (24 teams) in Malawi. A 1x1 factorial design will be used to assess the effect of the FIFA Football Nurse intervention. The two allocated groups will be the football teams’ (clusters) sport medicine practice. The teams will be randomly assigned to intervention or control. Prior to the commencement of the intervention, a survey will be sent out to the women’s football teams to explore the current state of healthcare provision and policies for management or referral of players with injuries or illnesses, knowledge of injury prevention programs as well as their present medical needs. Following this, a cohort of 12 general nurses will receive a one (1) day training in basic football medicine using the latest version of the FIFA Emergency Care training manual. This training will be conducted by experienced sports medicine personnel as well as experienced trainers in basic life support (BLS) and first aid from the Departments of Emergency and Orthopaedics at Kamuzu University of Health Science (KUHeS), Blantyre, Malawi. Following the training, the nurses will be attached to a total of 12 women’s football teams during one competitive season. They will also be given access to reference materials that are adapted from the FIFA Emergency Care manual.

The roles of the nurses within the teams will include menstrual, basic health, injury risk assessment, nutritional, and mental health assessment; on field assessment, basic life support; immediate care, and referral of injuries; as well as maintaining records of injuries, illnesses, medication use and football exposure using standardised instruments as previously used in other studies [35, 36].

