*Mental health assessment*. This will be assessed using the Sports Mental Health Assessment Screening Tool-1 (SMART-1). The SMART-1 is a standardised assessment tool that aims to identify individual athletes potentially at risk for or already experiencing mental health symptoms and disorders to facilitate timely referral for those in need of support or treatment [42].

*Football exposure*: *Injury*, *illness*, *and medication use surveillance*. These data will be collected at a cluster level using injury, illness and football load forms as recommended in injury consensus statements [36]. The research team will follow up with each football nurse on a weekly basis to ensure surveillance data is being captured. Should an injury occur that requires investigations or further management, the nurses will refer to the PT/Dr, who will proceed with the treatment, design/prescribe further management and document accordingly. League performance will also be collated from FAM at the end of the season as this has previously been associated with injury rates in other team sports [43].

Assessment of injury behaviours, team medical practice, injury risk, nutritional data, and mental health assessment will be done at three time points: at the beginning before the trial begins, halfway through the trial, and at the end of the season. Football exposure and surveillance data will be collected and collated at the end of each training session and/or match until the end of the season.

*Measurement of potential confounders*. Despite all players playing in the same league and at the same level, primary confounders for injury risk include physical/ anthropometric characteristics; existing mental health or psychiatric conditions and home environment, which may influence the SMHAT- 1 values, for example. Secondary confounders include playing experience, playing position, and playing level as well as socio-economic status, which will affect nutrition, menstrual hygiene management and private management of injuries. Where possible, these will be considered in the analyses. Some of them will also be explored further in the qualitative interviews at closure of the protocol.

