For the injury, illness, and medication use data, injury, illness, or medication use history will be recorded to determine the baseline injury, illness, or medication use risk. Injury, illness, and medication use rates and corresponding 95% CIs will be calculated for all players as the number of injuries/illnesses/medications reported per 1000 hours of football exposure (training and match). The severity of the injuries/illnesses, as scored by the number of days of missed training or matches, will also be calculated. Additional analysis will include, but not be limited to, the incidence and type of injury/illness/medication; chronic versus acute injuries/illnesses/medications; contact versus non-contact injuries and mechanism of injury (all per 1000 player hours). A Poisson regression will be used to compare differences in the injury, illness, or medication use rates between the control and intervention arms. To evaluate the impact of the FIFA Football nurse intervention on injury/illness/medication use outcomes, we will use logistic regression analysis to compare the proportion of players with injuries/illness/taking medications between the intervention and control arms, adjusting for potential confounding variables such as previous injury, age, playing experience, BMI, and playing conditions. We will also conduct subgroup analyses to determine whether the intervention has differential effects on different subgroups of players.

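### Injury, illness and medication events are found and recorded by different people in the two arms, so the planned between-arm rate and proportion comparisons mix any true effect with a detection difference

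*Protocol article*

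**What the plan says.** Under Standardisation of procedures, the two arms have different data collectors. For the intervention arm: "The football nurse attached to each team will be primarily responsible for data collection for the INT teams". For the control arm it is the research team that, "through a designated individual in the football team, will be responsible for data collection for the CON teams". The section on control or standard care identifies that individual: "A member of the research team will contact a designated member of their technical personnel to collect data on football exposure". The same sentence extends this to injury, illness and medication surveillance, with contact after every training session and league match.

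The description of the intervention in Materials and methods lists record keeping among the nurse's own duties, namely "maintaining records of injuries, illnesses, medication use and football exposure using standardised instruments". Under Secondary outcome measures, a check on data capture is described for the nurses: "The research team will follow up with each football nurse on a weekly basis to ensure surveillance data is being captured".

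The Data analysis paragraph expresses events per 1000 exposure hours, compares rates between arms by Poisson regression, and compares the proportions of players affected by logistic regression adjusted for player and playing-condition factors. It also scores severity by time lost: "The severity of the injuries/illnesses, as scored by the number of days of missed training or matches, will also be calculated".

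**The concern.** A rate comparison between randomised arms is interpretable only if an event has a similar chance of being recorded in each arm. Here the allocated arm decides who notices and writes down the event. One arm has a clinician attached for training and match cover. The other has a staff member who is probably not medically trained, since Table 2 excludes clubs "that already have medical personnel attached to their team".

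The hypothesis is that the nurse is superior to current practice. If she records more minor complaints, illnesses and medicines than a control contact would hear of, an effective programme could look neutral or harmful on these outcomes. The body of the protocol lists them as a secondary objective, although the abstract names injury and illness incidence within its primary objective. Who collected the data is fixed once the season is over, so a later analysis plan cannot repair it.

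**Working it through.** **No figure to reproduce.** The protocol states no capture rate or expected event rate for these outcomes. The check is a comparison of procedures, followed by an illustration.

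**Step 1: the arms side by side.**

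| | Intervention teams | Control teams |
|---|---|---|
| Who records | Attached nurse, who also delivers the intervention | Researcher, through a technical-staff contact |
| Medical background | Registered nurse | Probably none (inferred from the Table 2 exclusion) |
| When | After each session or match | After each session or league match |
| Follow-up stated | Weekly, by the research team | Researcher contact each time |

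Timing is close to equal. The recorder is not.

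**Step 2: do the stated safeguards equalise detection?**
- Consensus-statement forms and definitions govern how a noticed event is classified, not whether it is noticed.
- Biweekly monitoring of surveillance data checks that records are current and follow procedure.
- Coding the data before analysis (Blinding) comes after ascertainment.
- Adjustment for previous injury, age, experience, BMI and playing conditions cannot remove a difference that coincides with arm.

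None of them makes capture equal.

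**Step 3: illustration.** Let s_I and s_C be the shares of true events recorded in the intervention and control arms. With exposure hours measured correctly,

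observed rate ratio = true rate ratio × s_I / s_C.

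All shares below are assumptions; none comes from the documents.

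| True ratio | s_I | s_C | Observed ratio |
|---|---|---|---|
| 1.00 | 0.95 | 0.90 | 0.95/0.90 = 1.06 |
| 1.00 | 0.95 | 0.60 | 0.95/0.60 = 1.58 |
| 1.00 | 0.80 | 0.90 | 0.80/0.90 = 0.89 |
| 0.70 | 0.90 | 0.60 | 0.70 × 0.90/0.60 = 1.05 |
| 0.70 | 0.90 | 0.90 | 0.70 × 0.90/0.90 = 0.70 |

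The third row shows that the direction depends on the assumptions. The fourth shows a true 30% reduction disappearing. The last shows that equal capture leaves the ratio intact even when capture is incomplete. Proportions of players affected would also be distorted, though not by this simple factor.

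**Step 4: the denominator.** After describing nurse attendance records, the Adherence paragraph says: "These records will then allow for exposure hours to be calculated". Control teams have no nurse attendance to record. However, the control-arm section collects exposure after each session, and Secondary outcome measures refers to football load forms. These passages leave it unclear which source supplies exposure hours in the intervention arm.

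**The case against.** The strongest reply is that control data are collected promptly and in a structured way. A researcher makes contact after every session, forms and definitions follow consensus statements, and the biweekly monitoring is not limited to one arm. Weekly follow-up of nurses is, if anything, less frequent than the control contacts. Record keeping is openly part of the nurse's role, and the outcomes are secondary. All of this is correct, and it rules out describing the control data as distant recall. It does not answer the point that a nurse and a member of the technical staff may notice different things in the same session.

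Three stronger readings are tempting and are not supported.

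- **That the nurse biases the primary outcome.** A reader might infer this from the general sentence on data collection, which exempts nothing. The Primary outcome measure section makes the team practice questionnaire self-administered, and nothing says the nurse administers or completes it.
- **That control exposure hours are missing.** They are expressly collected. The Adherence wording needs reconciling and does not show a gap.
- **That the comparison reflects only who was looking.** It mixes true occurrence with detection, in proportions that the documents do not reveal.

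It is also fair to object that time loss is not independent of the nurse, whose assessment and referral may change days missed, and that a staff contact in an intervention team may learn of events because the nurse found them. Both are residual limits on the remedy.

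**Conclusion.** The point holds for the injury, illness and medication surveillance outcomes. The plan assigns different recorders by arm and then compares the arms directly, so a difference, or the absence of one, cannot be attributed to the intervention alone.

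The size cannot be computed from the documents. The range of 1.06 to 1.58 under a true null rests wholly on assumed capture of 95% against 60 to 90%, and a ratio below 1 is also possible. Over-recording by the nurse is plausible but not established. That the control contact is non-medical is an inference from the exclusion criteria.

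This should be fixed before the surveillance comparisons are used as evidence of effect. It does not reach the primary outcome as the protocol describes it.

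**What to change.** 1. **Endpoint.** In Data analysis, state that the between-arm comparisons of injury and illness rates and proportions use time-loss events, meaning those with days of training or matches missed, which the plan already scores. Label comparisons of all nurse-logged complaints, and of medication use, as descriptive. This costs only wording.

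2. **Common source, where feasible.** Extend the control arm's per-session technical-staff report to the 12 intervention teams, so that all 24 teams supply events and exposure hours in the same way. Keep the nurse log to describe activity in the intervention teams. The cost is a designated contact in each of those 12 teams and the extra researcher calls.

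3. **Exposure hours.** Reconcile the Adherence paragraph with the control-arm section and the load forms under Secondary outcome measures. Name one source of exposure hours for both arms and use nurse attendance for adherence only.

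The price is that fewer minor events enter the comparison, with some loss of precision. Time loss reduces detection bias without eliminating it, so the report should still say that recorders differed by arm.
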